### Data collection and management

This study will collect population data from eligible participants before the first treatment; these data include name, age, duration, occupation, blood pressure, sex, and body mass index (BMI). Drug and acupuncture adverse reactions will be recorded during the treatment and follow-up periods based on the reaction of the participants. At weeks 0, 12, and 24, data on carotid ultrasound, blood lipids, platelet aggregation, fibrinogen, platelet count, and apolipoprotein A-IV will be collected. The data collection will be performed by three staff members who will not take part in acupuncture treatment, index evaluation, statistical analysis, or grouping. The data collection and entry will be performed independently by two of the staff members and finalized by a third staff member. The main investigators, acupuncturist, sonographers, and laboratory staff will not be involved in data collection.

All data must be saved in paper with identification codes in seal, while electronic data is saved on the ResMan Research Manager of the Clinical Trial Management Public Platform, and photo formats are also named with identification codes to ensure authenticity and integrity. All data must be saved in paper, electronic, and photo formats to ensure authenticity and integrity. The data should be kept for at least 5 years after the article is published. A data monitoring committee was also set up in this study, composed of experts with good clinical research experience in the Department of Acupuncture of Guangdong Provincial Hospital of Traditional Chinese Medicine. Experts will regularly monitor research progress, data, participant management, distribution, and more. The committee is independent from the fund sponsor and has no conflicts of interest. Researchers who take charge in the data collection and entry will have access to the interim results and report to main investigators if necessary. Consequently, the main investigators will make the final decision to terminate the trial after discussion.

### Quality control

Before the study, all researchers will be required to accept uniform training. Researchers should be fully aware of the purpose and composition of this study. All acupuncturists will be required to have obtained a licence and have worked for more than 3 years. Before the study, acupuncturists will be trained to clarify the acupuncture standard in this study. During the study, the main investigator will check the CRF every week. The grouping, data collation, and data analysis will be carried out by specific staff members, and there will be no work intersect between these members. The adverse events that might occur during the study will be recorded in detail. The participants’ personal data will be kept by the researcher, and no one other than the researcher is allowed to access the data.

### Statistical analysis

This study will use per-protocol (PP) and intention-to-treat (ITT) analysis principles. ITT will include all subjects who participated in at least one treatment, including participants who dropped out. Missing data for participants who dropped out will be supplemented with the most recent data. The PP principle will analyse all participants’ data that conform to the study protocol, and those of individuals who did not conform to the protocol will not be included.

The data will be analysed by professional statisticians with SPSS 20.0 software (IBM SPSS Statistics, IBM Corp, Somers, NY, USA). First, we will describe the baseline data, such as age, blood pressure, course of the disease, BMI, and sex, and compare the baseline data between the three groups. The continuous variables will be presented as the mean ± standard deviation (SD), and the categorical variables will be presented as the composition ratio and rate.

Continuous variables that conform to a normal distribution will be analysed by ANOVA, and the non-conforming data will be analysed using the rank sum test. Categorical variables will be analysed using the chi-square (*χ*^2^) test or Fisher’s exact test. The confidence interval (CI) will be estimated at 95%, and the significance level will be set at 0.05. A *P* value < 0.05 will be considered statistically significant. The adverse data will be recorded and analysed for the relationship with acupuncture. We will calculate the dropout rate and analyse the reasons for dropping out.

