## Background

Atherosclerotic disease is a type of disease associated with arthritis, lipids, and other metabolic disorders in the body. Atherosclerotic disease is the main cause of cardiovascular and cerebrovascular diseases. According to research, in 2013 alone, 247.9 people died per 100,000 people due to these diseases, accounting for 28.2% of the total number of deaths [1]. Although the population structure has changed, the mortality rate of cardiovascular and cerebrovascular diseases has decreased by 22% [2]. A study found that one American dies every 1 min and 23 s from this type of disease, and a coronary event occurs every 34 s [3]. A 2009 study reported that the indirect and direct costs of cardiovascular disease and stroke in the USA were as high as $31 billion [4]. A study has counted the disease burden in China from 1990 to 2010. Among them, the main cause of death was stroke, and 1.7 million patients died of stroke in 2010. Ischaemic heart disease ranks second, with 948,700 cases of death from ischaemic heart disease, which both have intricate interactions with atherosclerosis [5].

For treatment, antiplatelet drugs and statins are often used in the clinic. Both antiplatelet drugs and statins can effectively reduce the incidence of cardiovascular and cerebrovascular diseases [6–9]. Additionally, aspirin combined with statins can reduce the incidence of cardiovascular events in patients with diabetes [10].

However, studies have found that antiplatelet drugs are not suitable for drug absorption and can cause gastrointestinal irritation and bleeding [11–13]. A survey found that 7–29% of patients taking statins developed myositis [14].

In a multi-centre study that included 2864 participants, the incidence of intracranial stenoses in patients with acute ischaemic stroke was 46.6%, of which 9.11% of cases were associated with carotid stenosis. Stroke patients with head and neck artery stenosis have more severe symptoms after admission and a higher prevalence of recurrent strokes. Head and neck arterial plaque should be an important intervention target for primary prevention before stroke [15].

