### Inclusion criteria

Conformation to the diagnostic criteria according to the Guidelines for Diagnosis and Treatment of Head and Neck Arteriosclerosis in China (2017) [20];No cardio-cerebrovascular diseases history;No vulnerable plaque and plaques on both sides that amount to less than five plaques;Cholesterol from 2.59 to 8.0 mmol/L and triglycerides (TGs) from 1.7 to 10.0 mmol/L;Age from 25 to 70 years old (unrestricted sex);No use of any medicine for atherosclerosis during the last 2 weeks;Agreement to participate the study and signed the informed consent before inclusion.

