### Randomization

Baseline data of participants will be collected within 2 weeks and evaluated before random assignment. Participants will be assigned to the TA group, the MC group, or the SA group at a ratio of 1:1:1. To ensure the equality of random distribution, the generation of random sequences will be performed by the Acupuncture Research Institute, who will not participate in this study. Random numbers and grouping results will be saved in opaque envelopes by the staff who performed the randomization. All envelopes will be kept by staff who will not participate in the study. The research assistant will open the envelopes to assign them in the order in which they are registered.

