### Blinding

Because of the characteristics of acupuncture, the acupuncturists in this study cannot be blinded to the assignment, but the participants can be blinded. The treatment, testing, and follow-up of each group will be implemented independently, with no intersection between each group. The sham acupuncture in this study can guarantee a painful effect, similar to acupuncture, but does not penetrate the skin; sham acupuncture will allow for the better blinding of the participants. In addition, participants in the TA and SA groups will be asked three questions at the end of the 12 weeks to test the blinding effect: ‘Do you have confidence in this treatment?’ ‘Would you recommend this therapy to your friends?’ ‘Can you accept this kind of acupuncture?’ The participants will choose ‘Yes’ or ‘No’ to answer the questions. The data will be analysed at the end of the study. If the results are not significant, then it can be concluded that the blinding was sufficient. To ensure the uniformity of ultrasound examination and blood testing, all ultrasound examinations will be completed by a doctor with over 10 years of vascular ultrasound work experience. The Department of Clinical Laboratory of Guangdong Provincial Hospital of Traditional Chinese Medicine is responsible for the whole blood testing process. Both the ultrasound doctor and clinical laboratory will be blinded to the assignment. Collectors and statisticians responsible for collecting data and statistics will be blinded to the assignment.

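### The set called ITT leaves out randomised participants who never start treatment, and that loss can differ between the medication arm and the two needle arms

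*Protocol article*

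**What the plan says.** The protocol article names two analysis sets, in the Abstract and again under Statistical analysis.

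- **ITT:** "ITT will include all subjects who participated in at least one treatment, including participants who dropped out".
- **PP:** only data that follow the protocol are used, and "those of individuals who did not conform to the protocol will not be included".
- **Missing values:** "Missing data for participants who dropped out will be supplemented with the most recent data".

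No set of all randomised participants is defined. The same section says that a dropout rate will be calculated and the reasons examined.

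On the order of events, the Randomization section says "Baseline data of participants will be collected within 2 weeks and evaluated before random assignment", and then "The research assistant will open the envelopes to assign them in the order in which they are registered".

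On masking, the Blinding section says "the acupuncturists in this study cannot be blinded to the assignment, but the participants can be blinded". The device that achieves this is the blunt sham needle, and the end-of-treatment questions on blinding go to TA and SA only. The MC group section describes named tablets and mentions no dummy procedure.

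**The concern.** Intention-to-treat analysis keeps the groups that randomisation made. A set that requires at least one treatment adds a condition that can only be met after assignment. If that condition is met equally often, and by the same kind of person, in every arm, little is lost. If it depends on the arm, the groups compared are no longer those that were randomised, and the confidence interval gives no sign of it.

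Here it could depend on the arm. TA and SA are meant to look alike to the participant, while MC is plainly different. Some participants are recruited through acupuncture departments, and free acupuncture after follow-up is promised to SA only. Someone who joined hoping for needling and is assigned tablets may not begin.

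The Study design section sets MC up as the positive control against which acupuncture is judged. TA versus MC is therefore one of the trial's stated purposes, and it is one of the two comparisons affected. The result would also be reported as ITT when it is not.

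**Working it through.** **1. The plan's own figure.** The Sample size section takes 30 per group and an expected maximum dropout of about 15%, and arrives at 35 per group, 105 in total. This reproduces as 30 × 1.15 = 34.5, rounded up to 35, and 3 × 35 = 105. (Dividing instead, 30 / 0.85 = 35.3, gives 36 per group and 108. The difference is one per group and does not bear on this point.) The arm size used below is 35.

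**2. Where a never-starter goes.**

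- In the ITT set? No: at least one treatment is required.
- In the PP set? No: this person did not follow the protocol.
- In any other efficacy set? None is defined.
- Does the person have data? Yes: baseline is collected before assignment, so week 0 values exist for everyone randomised.

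**3. Can never starting depend on the arm?** An MC participant receives named tablets and no needling, so the arm is known at the first dose at the latest. TA and SA participants are meant not to be able to tell their arms apart. Participant knowledge can therefore separate MC from the needle arms, but not TA from SA.

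**4. Is the entry condition clear for MC?** The Intervention section counts treatments for the groups as two per week, 24 in all. The MC group section describes tablets taken daily and handed out weekly, and says only that missed or stopped tablets are recorded. Whether one tablet, one weekly supply or something else makes one treatment in MC is not stated.

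**5. Size.** Let m be the number of MC participants who never start, and d their mean difference from starters in SD units of the outcome. Neither is in the document; both are assumed.

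Shift in the MC mean = (m / 35) × d

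| m | MC set left | Share of arm lost | d = 0.25 | d = 0.5 | d = 1.0 |
|---|---|---|---|---|---|
| 1 | 34 | 2.9% | 0.007 | 0.014 | 0.029 |
| 2 | 33 | 5.7% | 0.014 | 0.029 | 0.057 |
| 3 | 32 | 8.6% | 0.021 | 0.043 | 0.086 |
| 5 | 30 | 14.3% | 0.036 | 0.071 | 0.143 |

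For scale, the standard error of a two-arm difference at 35 per arm is √(2/35) = 0.239 SD. With 30 left in MC it is √(1/35 + 1/30) = 0.249 SD. The largest shift in the table is 0.143 / 0.239 = 0.60 of a standard error.

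**6. What the missing-data rule would do once these people are included.** If a never-starter gives no week 12 or 24 data, the most recent value is the week 0 value, so the change from baseline is set to zero. The MC mean change is then the starters' mean change multiplied by (35 − m) / 35: 0.971 for m = 1, 0.914 for m = 3 and 0.857 for m = 5.

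**The case against.** The case against making much of this is fair in several respects.

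- **Disclosure.** A reader might infer that participants see their envelope and then have time to decline. The article does not say so: the research assistant opens the envelopes, and neither the moment of telling participants nor any gap before treatment is described. What stands is narrower: the MC arm is recognisable by the first dose.
- **Disappearance.** A reader might infer that never-starters leave the trial record altogether. They leave both efficacy sets, but may still appear in the promised dropout count and reasons.
- **Side effects as evidence.** The Background states "A survey found that 7–29% of patients taking statins developed myositis [14]". That figure, like the gastrointestinal effects cited beside it, concerns people already taking the drugs. Anyone who stops after starting stays in the set as defined, so these figures do not show that anyone fails to start.
- **Who enters.** The criterion "No use of any medicine for atherosclerosis during the last 2 weeks" might be read as selecting people who avoid these drugs. Nothing in the article supports that. Recruitment also covers physical examination and cardiovascular departments and a volunteer platform, and the same pool feeds all three arms.
- **Consent.** Participants are told about treatments and risks before enrolment and sign consent before inclusion. That should lower refusal after assignment, though it cannot rule it out. A further check of willingness would largely repeat it.
- **Drug screening.** A reader might turn this into a point about screening for earlier drug intolerance. That is a clinical eligibility matter, the exclusion list already names some relevant conditions, and the analysis-set point does not need it.
- **Size and purpose.** This is a pilot, and the shifts above are small beside sampling error even with unfavourable assumptions.

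None of this alters the definition itself. The set is conditional on treatment, it is called ITT, and no other set brings the missing people back.

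**Conclusion.** The point holds as one about the definition and label of an analysis set. The ITT set is a modified ITT set, and a randomised participant who never starts is in neither stated set. Because MC is recognisable, the loss may differ between MC and the needle arms, so TA versus MC and SA versus MC may not compare the groups as randomised. TA versus SA is not exposed through participant knowledge.

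That uneven loss can occur follows from the text; that it will occur is not shown. With no number of never-starters in the article, the size of the bias is unknown. On the assumed inputs it is probably small next to sampling error. The finding does not support calling the comparisons invalid. It supports correcting the definition before the analysis is done.

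**What to change.** In the Statistical analysis section:

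1. Define ITT as all randomised participants, analysed in the arm assigned, whether or not treatment began.
2. Rename the present set modified ITT and keep it as a sensitivity set.
3. State what counts as one treatment in MC, so that membership of that set can be decided in the same way in every arm.
4. Report the number of never-starters by arm, with reasons.
5. Ask never-starters to attend the week 12 and week 24 assessments. Where these are not obtained, state openly that carrying forward the most recent value gives them zero change from baseline, and report this as an assumption.

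**Cost.** Mostly wording. Baseline data already exist for everyone randomised. A few outcome visits would be sought from people who never began treatment, and the effect estimate may be slightly diluted. The Trial status section reports 42 participants by October 2019. The change can still be made before analysis and needs no alteration to eligibility or the envelope procedure, so it does not create two entry regimes. It should be reported to the ethics committee and the registry, as the Ethics and dissemination section requires for protocol changes.

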### Ethics and dissemination

The study was planned in accordance with the Declaration of Helsinki. This study was approved by the Institutional Ethics Committee of Guangdong Provincial Hospital of Traditional Chinese Medicine (approval no. YF2018-107-01). Trial has been registered at the Chinese Clinical Trial Registry (ChiCTR1800019259). If there is any change to the clinical research protocol and informed consent, the researchers will be asked to report the modifications to both the ethics committee and registry centre timely.

Before the participants are enrolled in the study, the researchers will fully inform the patient of the treatment and tests that need to be completed and fully inform the participant regarding the risks that may exist in the study and their power to withdraw from the study. Patients are also informed enough to understand the possible adverse reactions of collecting biological specimens. All treatments and tests in this study will be provided for free. Throughout the research process, we will provide free medical advice and guidance to all participants. After all follow-ups, we will provide 3 months of free acupuncture treatment for participants in the SA group. The participants will also be paid for part of their travel expenses to and from the hospital, all of which will be offered to enhance participant compliance.

### Patients and public involvement

An acupuncture patient originally proposed acupuncture treatment for carotid atherosclerotic plaque. None of the other participants in the study participated in the design or evaluation. The burden of the intervention will be assessed by the patients themselves. The results will be disseminated to study participants via email or phone messages.

### Trial status

The trial is currently in the recruitment phase. The protocol is registered on November 1, 2018. The protocol number is ChiCTR1800019259. The recruitment started on July 1, 2018, and as of October 2019, a total of 42 people had participated in the study. The expected date of trial completion is June 30, 2020.

## Discussion

The rupture of carotid atherosclerotic plaque is one of the risk factors for cerebrovascular disease, and a clinical emphasis has been placed on the early treatment and prevention of cardiovascular events [28]. Although clinical antiplatelet aggregation and lipid-lowering drugs have been widely used, the side effects of drugs are still difficult to avoid. Therefore, we hope this pilot study could provide an effective data basis for subsequent large-sample studies of acupuncture treatment for atherosclerotic plaque.

### Comprehensive selection of outcome measures

Doppler ultrasound technology is an economical, simple, non-invasive detection method that is widely used for carotid atherosclerotic plaque and stenosis detection. The vessel plaque quantification technique used in this study can assess PV, plaque composition, and plaque remodelling structure.

The GSM value is an average evaluation of the plaque on one side of the carotid artery, which can effectively evaluate the components of the plaque. The lower the GSM value, the higher the lipid content in the plaque, and the higher the GSM value, the higher the calcium and fibre content in the plaque [24]. The GSM value of the plaque is related to plaque stability, and plaques with high lipid content usually have higher instability.

Lipid metabolism plays a key role in plaque elimination. HDL has anti-atherosclerosis effects, and its concentration is negatively correlated with the occurrence and severity of atherosclerosis. The main component of HDL is apolipoprotein A-I (70%), followed by apolipoprotein A-II and apolipoprotein A-IV. In this study, we will observe whether acupuncture plays an anti-atherosclerotic plaque role by regulating blood lipid levels.

In terms of coagulation-related indicators, most scientists believe that inflammation can stimulate the vascular endothelium to activate platelets and promote the binding of platelets to fibrinogen, thereby promoting arteriosclerotic thrombosis. Our previous study revealed that apolipoprotein A-IV is a new ligand for platelet GPIIβ/IIIα integrin, which competitively inhibits the binding of glycoprotein GPIIβ/IIIα to fibrinogen and inhibits platelet aggregation [27, 29]. In this study, platelet function will be used as an entry point to explore whether acupuncture can antagonize the binding of platelets to fibrinogen by changing the level of apolipoprotein A-IV, thereby reducing the PAR in blood and reducing the formation of plaque. Figure 5 shows the way in which acupuncture may affect apolipoprotein A-IV.

**Fig. 5 Fig5:**
[figure not shown]
The potential influence that acupuncture works on Apo A-IV level. Acupuncture may antagonize the binding of platelets to fibrinogen by changing the level of apolipoprotein A-IV, thereby reducing the PAR in blood and reducing the formation of plaque

### Selection of medication and placebo acupuncture method

There are different methods for the sham group based on acupuncture research, such as superficial skin acupuncture, non-acupoint acupuncture, and random acupoint acupuncture. According to the purpose of this study, we will adopt blunt needle acupuncture, which can avoid the effect of acupuncture epidermis therapy, and the design is more rigorous.

For drug selection, this study will use aspirin plus statins. The US 2014 AHA/ASA first-line prevention guidelines for stroke recommended that patients with asymptomatic carotid stenosis take aspirin or statin drugs [30]. Previous studies have suggested that the recommended dose of long-term aspirin is 75–150 mg/day. Most participants in this study are mild symptomatic carotid atherosclerotic plaque patients, which is consistent with the primary prevention of stroke. Based on the opinions of the Ethics Committee of the Guangdong Provincial Hospital of Traditional Chinese Medicine and patient’s risk factors, the dose of aspirin was adjusted to 100 mg/day. Statins exert beneficial effects for arteriosclerosis patients by reducing blood lipids and stabilizing plaques. According to the systematic analysis of the effects of different doses of atorvastatin on Chinese carotid artery stenosis (CAS) patients, patients taking 10 mg/day suffered fewer side effects, such as transverse muscle dissolution and elevated transaminase, while the treatment effect showed no significant difference. From an ethical point of view, the clinical dose of atorvastatin used in this trial is 10 mg/day after discussion.

